# Person-centred transition programme to empower adolescents with congenital heart disease in the transition to adulthood: a study protocol for a hybrid randomised controlled trial (STEPSTONES project)

**DOI:** 10.1136/bmjopen-2016-014593

**Published:** 2017-04-17

**Keywords:** Adolescents, Heart defect, Person centered care, Randomized controlled trial, Transition

## Abstract

**Introduction:**

When a young person grows up, they evolve from an independent child to an empowered adult. If an individual has a chronic condition, this additional burden may hamper adequate development and independence. Transition programmes for young persons with chronic disorders aim to provide the necessary skills for self-management and participation in care. However, strong evidence on the effects of these interventions is lacking. Therefore, as part of the STEPSTONES project (Swedish Transition Effects Project Supporting Teenagers with chrONic mEdical conditionS), we propose a trial to assess the effectiveness of a structured, person-centred transition programme to empower adolescents with congenital heart disease in the transition to adulthood.

**Methods/design:**

STEPSTONES will use a hybrid experimental design in which a randomised controlled trial is embedded in a longitudinal, observational study. It will be conducted in 4 paediatric cardiology centres in Sweden. 2 centres will be allocated to the randomised controlled trial group, assigning patients randomly to the intervention group (n=63) or the comparison group (n=63). The other 2 centres will form the intervention-naïve control group (n=63). The primary outcome is the level of patient empowerment, as measured by the Gothenburg Young Persons Empowerment Scale (GYPES).

**Ethics and dissemination:**

The study has been approved by the Regional Ethical Board of Gothenburg, Sweden. Findings will be reported following the CONSORT statement and disseminated at international conferences and as published papers in peer-reviewed journals.

**Trial registration number:**

NCT02675361; pre-results.

Strengths and limitations of this study
This is a multicentre study that uses a novel study design to test the effectiveness of a person-centred transition programme.Although several guidelines have recommended the implementation of transition interventions, the evidence of these is still insufficient. The study is expected to fill a gap in current transitional care knowledge.Owing to the type of intervention, blinding of participants is not possible.In order to have a long follow-up, transition interventions are recommended to start before the age of 16 years, which is not feasible in this study.

## Background

In developed countries, 10–40% of the adolescent population has a chronic disease with childhood onset.^1^ As a result of improvements in diagnostic techniques and treatments, survival has increased, and 90% of them now reach adulthood.^2^ Growing up with a chronic condition poses an extra burden on the individual, over and above the challenges typically related to adolescence. Management of the transition from childhood to adulthood and the shift from paediatric to adult care requires special attention from healthcare professionals. The movement to adult care is known as transfer, defined as “an event or series of events through which adolescents and young adults with chronic physical and medical conditions move their care from a pediatric to an adult health care environment”.^3^ This transfer should be preceded by a preparatory transitional phase. In healthcare, transition can be defined as the “process by which adolescents and young adults with chronic childhood illnesses are prepared to take charge of their lives and their health in adulthood”.^3^ To improve and facilitate this process, transition programmes have been developed.^4^ A well-designed transition programme is individually tailored, flexible, and age and developmentally appropriate.^5^ The goal of transition programmes is to support the person's adjustment to a new care culture, to provide the necessary tools for self-care and to help satisfy medical, psychosocial and educational needs.^6^ Evidence on the effects of transition programmes is scant, the level of existing evidence is low and the effectiveness of these interventions has yet to be determined.^7^ This is due to the limited number of effectiveness studies; methodological issues (eg, contamination of control groups has not been accounted for in prior studies) and a short follow-up period of 12 months maximum.^7^

Patient empowerment is an asset that relates to the adolescents' self-management and participation in care.^8^ Empowered adolescents can interact better with the adult healthcare system, and are more independent and more actively involved in decisions regarding their health.^9^
^10^ However, patient empowerment has not been a formal target in transition programmes so far. To increase the level of empowerment, a person-centred care (PCC) approach is important.^11^ This perspective allows for a partnership between the adolescent and healthcare providers in which the adolescent's views guide the intervention.^12^ Through this approach, it is possible to share helpful resources and information with the adolescents and give them the opportunity to assume an active role in the decision-making process.^11^

Congenital heart disease (CHD) is a typical example of a life-course disease and can therefore be considered a chronic condition. CHD has a prevalence of 9.1 per 1000 newborns and represents 28% of all congenital defects.^13^ Around 90% of children born with CHD reach adulthood,^2^ and ∼6.2 in 1000 adults live with this condition.^14^ Although several centres have established a transition programme for individuals with CHD,^15^ only one study on the effectiveness of such a programme has been undertaken so far. That study was conducted in Canada and used a quasi-experimental design to test the effects of a 1-hour intervention led by a nurse.^16^ Significant improvements in the level of knowledge and self-management among patients were observed.^16^ In addition, a comparative and a longitudinal study in Belgium confirmed the effectiveness of patient education.^17^
^18^

To address the gaps in evidence on the effectiveness of transition programmes, we established the STEPSTONES project (Swedish Transition Effects Project Supporting Teenagers with chrONic mEdical conditionS). This project aims at developing and evaluating the effectiveness of transition programmes for young persons with chronic childhood-onset conditions. Although the project will encompass different chronic conditions, it will first study adolescents with CHD.

### Objective and hypothesis

This article describes the protocol for a study to test the effectiveness of a transition programme to empower adolescents with CHD in the transition to adulthood and the transfer to adult care. The main hypothesis is that adolescents with CHD who receive a structured, person-centred transition programme over a 2-year period have a higher patient empowerment score than adolescents receiving usual care.

This study is presented in accordance with the guidelines issued by SPIRIT for reporting of study protocols.^19^

## Methods/design

### Study design and setting

A hybrid experimental design will be used, in which a randomised controlled trial (RCT) is embedded in a longitudinal, observational study. This will result in a three-arm design (see figure 1). The study will be conducted in four CHD centres in Sweden. Two of the centres are allocated to the RCT, where participants are randomly assigned to either the intervention group or the comparison group. The other two centres are designated as the control group and represent intervention-naïve centres.

**Figure 1 BMJOPEN2016014593F1:**
[figure not shown]
Overview of the study design and implementation steps.

This type of design allows for the investigation of the effectiveness of the transition programme while also taking into account potential contamination of the comparison group in the intervention centres.

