### Sample size estimation

Sample size calculation is based on the primary outcome of patient empowerment. The target is an improved patient empowerment score of 5.25 points on a scale from 15 to 75 (ie, 0.5 SD). For two-sided tests with α=0.05 and power=80%, 63 patients are needed in each arm of the RCT. In order to compensate for a potential 10% dropout rate, we will recruit 70 patients in each arm of the RCT. An additional 70 patients will be recruited in the centres of the control group. Among the four centres, a total of 210 patients will be enrolled (see figure 1).

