### Randomisation

Using a web-based system, a stratified block randomisation with a random variable block size will assign patients of the RCT centres to the intervention group or the comparison group (1:1).^21^ Block randomisation ensures that the TCs in the two centres have a relatively continuous exposure to the intervention over time, which allows them to keep their skills up to date and to ensure the fidelity of the intervention. The fact that the block sizes vary randomly minimises the possibility that the TCs could predict group assignments.

Stratification is made by centre and disease complexity. The stratification for centre ensures that the two centres have an equal number of intervention patients. Stratification by disease complexity (mild; moderate; complex)^22^ is important to avoid over-representation of those people with, for example, complex CHD in one or the other group due to failing randomisation.

Overall, this approach decreases the within-centres variability and reduces the risk for bias and confounding.^21^ The TCs are responsible for accessing the randomisation system in order to determine patient allocation.

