#### Usual care (intervention, control and comparison group)

All adolescents who participate in the study receive usual care, irrespective of whether in the intervention, comparison or control group. Usual care includes visits to an outpatient paediatric cardiology clinic where they meet a nurse and a paediatric cardiologist. Disease complexity determines the frequency of the visits. None of the participating centres have a TC as a part of usual care and there is no documentation of transition plans. It is common practice in Sweden that patients are transferred to adult care around the age of 18 years.

Since usual care can vary across clinics and over time, an assessment of transition-related practices will be carried out in all the centres at the beginning of the intervention and at the end of the study. This assessment will comprise three elements: (1) a structured survey called CHAT (Congenital Heart Adolescent and Transition; on file); (2) interviews with healthcare professionals who are involved in the care for adolescents with CHD in the participating centres and (3) observations of the routine during the clinic visits.

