Second, the proposed hybrid experimental design allows us to account for potential contamination of the control group. Indeed, the three arms allow performance of direct comparison between the intervention and comparison group while enabling a comparison of findings with those obtained in intervention-naive centres.

Third, patient empowerment is used as the primary outcome. Empowerment is argued to be important for the development and application of skills to promote behavioural changes in the adolescents.^10^ Admittedly, empowerment can be seen both as a process and an outcome.^10^ However, being an intermediate outcome, empowerment can be argued to be proximal to the intervention, whereas continuing cardiac care, reduced morbidity or mortality are probably the ultimate, but more distal outcomes.

Fourth, the PCC approach that is used throughout the transition programme is an important asset in the process of empowering patients.^11^ Providing transitional care from a person-centred perspective is novel and has not been evaluated before in this age group.

Fifth, we follow-up the patients for more than 2 years. While doing so, we substantially expand the follow-up period of 12 months as used in prior studies.^7^

Sixth, since usual care may vary across centres and over time, we carry out a formal usual care assessment. Such a usual care assessment is important to draw firm conclusions, and yet this is seldom performed in clinical trials.^50^

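### The control-centre arm is a descriptive benchmark: with two non-randomised centres on each side, contamination cannot be separated from centre, so the design does not account for it

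*Protocol article*

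**What the plan says.** The claim appears twice in the protocol article. Under Study design and setting, in the sentence after Figure 1, the design is said to allow a test of effectiveness "while also taking into account potential contamination of the comparison group in the intervention centres". The Discussion gives as the second strength that "the proposed hybrid experimental design allows us to account for potential contamination of the control group", and explains that results can be set beside those from intervention-naïve centres. The Background criticises earlier studies for not dealing with contamination, so this is a main justification for the third arm.

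The structure behind the claim is as follows.

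- Study design and setting: "The study will be conducted in four CHD centres in Sweden". Two take part in the RCT. "The other two centres are designated as the control group and represent intervention-naïve centres".
- Randomisation: only patients of the two RCT centres are randomised, 1:1, stratified by centre and disease complexity. No random allocation of centres is described.
- Sample size estimation: 63 per RCT arm, raised to 70 for dropout, and a further 70 in the control centres.
- Usual care: "Since usual care can vary across clinics and over time", transition practice is assessed in all centres at the start of the intervention and at the end of the study by survey, interviews and observation.

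The limitations listed in the Discussion do not qualify the contamination claim.

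**The concern.** The outcome contrast that the third arm adds is comparison group versus control group. If the programme leaks within the RCT centres, comparison patients should end higher than patients in centres that never had it. That inference needs the two pairs of centres to be alike apart from the leak. Nothing in the design secures this, and the Usual care section expects practice to differ between clinics and to change over time.

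What is at stake is the interpretation of the trial, above all if the randomised result is null or small. A comparison-control difference close to zero does not show that the comparison group was clean. A difference in favour of the comparison group does not show leakage. Presented as a design that accounts for contamination, the third arm lends support to either reading that it cannot give.

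**Working it through.** **Inputs from the protocol.** Target 5.25 points = 0.5 SD, so SD = 5.25/0.5 = 10.5. Two-sided α = 0.05, power 80%, 63 per arm, 10% dropout. Two centres on each side of the comparison-control contrast.

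**Assumed, because the protocol gives no figure.** ICC for centre 0, 0.02 and 0.05; leakage of 20% or 30% of the target effect; equal centre sizes; where baseline adjustment is considered, a T0-T2 correlation of 0.5.

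**1. The plan's own figure.** n = 2(1.960 + 0.842)²/0.5² = 62.8, so 63 per arm, and 63/0.90 = 70. Both reproduce. They concern the randomised contrast and are correct for it.

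**2. Identification.** A model with three arms and four centres has 1 + 2 + 3 = 6 columns but rank 5. The control-arm indicator is the sum of the indicators of its two centres. With centre in the model the comparison-control contrast cannot be estimated; with centre left out, the contrast contains the centre differences. This does not depend on sample size or on any analysis plan.

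**3. What baseline scores can do.** T0 GYPES is measured in all groups, so an analysis adjusted for it can remove centre differences that stay constant. A centre whose usual care changes between T0 and T2 produces the same pattern as leakage.

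**4. Precision with centre ignored (the most favourable case).** SE = 10.5 × √(2/63) = 1.87. The 95% half-width is 1.96 × 1.87 = 3.67 points, and 3.67/5.25 = 70% of the target effect. Power to see a leak:

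| Leak (assumed) | Points | Power |
|---|---|---|
| 20% | 1.05 (d = 0.10) | 9% |
| 30% | 1.575 (d = 0.15) | 13% |

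**5. Precision with centre as the unit.** Var = SD² × [2 × ICC/2 + 2 × (1 − ICC)/63], with 4 − 2 = 2 df and multiplier 4.303.

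| ICC (assumed) | Var | SE | 95% half-width |
|---|---|---|---|
| 0 | 110.25 × 0.0317 = 3.50 | 1.87 | 8.0 |
| 0.02 | 110.25 × (0.0200 + 0.0311) = 5.64 | 2.37 | 10.2 |
| 0.05 | 110.25 × (0.0500 + 0.0302) = 8.84 | 2.97 | 12.8 |

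Using 1.96 with the last two SEs would give 4.7 and 5.8 points, but that treats the between-centre variance as known, which four centres do not allow.

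**6. Does baseline adjustment rescue precision?** With r = 0.5 the patient-level variance is multiplied by 1 − 0.25 = 0.75. If the remaining centre variance is unchanged, the half-widths on 2 df are 7.0, 9.4 and 12.2 points. They would be smaller if adjustment also removed centre variance, but even at ICC 0 the value exceeds the 5.25-point target.

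**7. Would more patients help?** With unlimited patients the SE tends to SD × √ICC. At ICC 0.05 this is 10.5 × 0.2236 = 2.35, a half-width of 4.303 × 2.35 = 10.1 points. The limit is the number of centres.

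**8. A patient-level test that ignores centre.** With no leak at all, it would reject in 2 × [1 − Φ(1.96 × 1.87/2.97)] = 22% of trials at ICC 0.05.

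**The case against.** The protocol's wording is modest. The Discussion glosses the claim as allowing findings to be compared with those from intervention-naïve centres, and Study design and setting already calls the surrounding study longitudinal and observational. Contamination is also handled by other means: coordinators do not care for comparison patients, other staff are not told the components, and usual care is assessed in every centre at start and end. The ICC and leakage values above are assumptions.

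Much of this stands. The separation of staff may reduce leakage, although it does not measure it. The usual-care assessment is real evidence on contamination, so it would be wrong to say that the comparison-control contrast is the only place to look. The identification argument in step 2 needs none of the assumed values.

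A reader might infer more than the protocol supports:

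- *That the trial will declare contamination present or absent from a significance test.* No such rule is stated.
- *That the lack of a model for the third arm, or of a precision-based size for it, is a defect.* The protocol defers its analyses to a statistical analysis plan that is not shown, so neither counts here.
- *That the 80% power is overstated because leakage dilutes the effect.* If 5.25 points were the undiluted effect, a 20% or 30% leak would reduce power to 61% or 50%. The sample size section does not say whether the target is before or after dilution, so the figure cannot be called wrong.

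What remains is that both statements present accounting for contamination as something the design achieves, with no caveat about centre.

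**Conclusion.** The claim is wrong as worded and should be restated. The comparison-control contrast mixes contamination with centre, case-mix and centre-specific change in usual care, and no analysis plan can undo this with two designated centres a side. That part rests only on the protocol's own description.

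The imprecision is secondary and partly assumed. The 3.7-point half-width follows from the protocol's figures with centre ignored. The 8.0 points on 2 df assumes no centre variance, and the 10.2 and 12.8 points need the assumed ICCs. The 9% and 13% powers need the assumed leakage and ignore centre.

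The randomised intervention-comparison contrast remains valid, its 63 per arm is correct, and the primary conclusion does not depend on the third arm. It would be a mistake to read this point as undermining the RCT. Contamination could dilute the randomised difference; the third arm cannot establish by how much.

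**What to change.** 1. In Study design and setting and in the Discussion, replace the statements that the design accounts for contamination. Say that the control-centre comparison is a descriptive, observational benchmark confounded with centre, and that the randomised difference is the effect estimate and may be diluted by contamination.
2. Report comparison versus control at T2, adjusted for T0 GYPES and disease complexity, as an estimate with an interval that reflects between-centre variation (for example a t interval on 2 df from centre-level adjusted means). A patient-level interval would repeat the problem. Attach no significance verdict on contamination.
3. Base the judgement on contamination mainly on within-centre change in the usual-care assessment (survey, interviews, observation) already planned at start and end.

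The cost is some wording, a little extra analysis and a less favourable claim for the design, with a visibly wide interval. No new data, patients or centres are needed.

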### Sample size estimation

Sample size calculation is based on the primary outcome of patient empowerment. The target is an improved patient empowerment score of 5.25 points on a scale from 15 to 75 (ie, 0.5 SD). For two-sided tests with α=0.05 and power=80%, 63 patients are needed in each arm of the RCT. In order to compensate for a potential 10% dropout rate, we will recruit 70 patients in each arm of the RCT. An additional 70 patients will be recruited in the centres of the control group. Among the four centres, a total of 210 patients will be enrolled (see figure 1).

### Participants and recruitment

Eligible participants are (1) adolescents with CHD, defined as “a gross structural abnormality of the heart or the intrathoracic great vessels that is actually or potentially of functional significance”;^20^ (2) age 16 years; (3) Swedish speaking and (4) literate.

Patients are excluded if they do not have the physical or cognitive capacity to complete the questionnaires, or have acquired heart conditions or heart transplantation. Parents of the adolescents will also be asked to participate. All eligible participants are recruited by a transition coordinator (TC) or a data collection officer (DCO).

### Randomisation

Using a web-based system, a stratified block randomisation with a random variable block size will assign patients of the RCT centres to the intervention group or the comparison group (1:1).^21^ Block randomisation ensures that the TCs in the two centres have a relatively continuous exposure to the intervention over time, which allows them to keep their skills up to date and to ensure the fidelity of the intervention. The fact that the block sizes vary randomly minimises the possibility that the TCs could predict group assignments.

Stratification is made by centre and disease complexity. The stratification for centre ensures that the two centres have an equal number of intervention patients. Stratification by disease complexity (mild; moderate; complex)^22^ is important to avoid over-representation of those people with, for example, complex CHD in one or the other group due to failing randomisation.

Overall, this approach decreases the within-centres variability and reduces the risk for bias and confounding.^21^ The TCs are responsible for accessing the randomisation system in order to determine patient allocation.

